### Participants

#### Inclusion criteria

We will include individuals with ID aged 18 years or over who have mild or moderate ID (IQ of 35–60) assessed using the Wechsler Abbreviated Scale of Intelligence, Second Edition,^29^ should not be attending college/education or a day service for 3 or more days a week; will have a score of 5 or more on the Glasgow Depression Scale for People with Learning Disability (GDS-LD^28^), indicating the presence of depressive symptoms but do not need to have a clinical diagnosis of depression. Participants will need to be able to speak English and provide informed consent.

Volunteers will be aged 18 years or over, who can agree to being available once a week for at least 1 hour over a period of 6 months. Volunteers do not need to have any prior experience of supporting people with ID.

#### Exclusion criteria

Individuals with ID will be excluded if they have limited communication and comprehension and therefore would not be able to complete the questionnaires.

Volunteers will be excluded if they have a criminal record (any documented offence due to the vulnerability of this population) recorded on their Disclosure and Barring Service (DBS) check or are unable to provide two references or have unsuitable references.

### Recruitment

#### Befriending services

Two befriending services (‘Outward’, based in Hackney, North London, and ‘the befriending scheme’ in Suffolk) will be taking part in the study and will be responsible for overseeing the befriending intervention. Both services have experience supporting befriending relationships with people with ID, including matching individuals with volunteers and monitoring relationships.

#### Participants with ID

Participants with ID will be recruited from existing and new referrals to the befriending services or recruited from the caseload of clinicians working in community learning disability services at the North East London NHS Foundation Trust (NELFT) and Suffolk. Volunteer coordinators and clinicians will screen referrals and caseloads for participants who may be eligible for the study and will make the initial approach. If the individual is interested in the study and consents to his/her details being passed on to the research team, a referral form will be completed and emailed to the research team. The research assistant (RA) will then contact the individual and carry out an eligibility assessment. If the individual is eligible, they will need to provide written consent before completing the baseline assessment.

#### Volunteers

The befriending services will advertise and recruit volunteers through newspaper advertisements, befriending and job websites, social media, and recruitment events at colleges and universities. Volunteers will be recruited directly from the study website hosted by the UCL Division of Psychiatry and through the Division’s twitter account. Interested volunteers will complete an application form and will be invited to an informal interview to assess their suitability and motivation for taking part in the scheme. A DBS check will be completed to ensure that they have no criminal records, and references will be obtained. People with ID are potentially a vulnerable group, and therefore, volunteers with any previous offence, including minor offences, will not be included in the study. Successful candidates will be invited to take part in the study. They will receive an information sheet and will be asked to sign a consent form, followed by completion of the baseline assessment.

### Randomisation

Randomisation will be carried out after the baseline assessments have taken place. Participants will be randomised into the study by an unblinded member of the research team who will enter the patients’ details into a web-based randomisation system, which is hosted on a secure server by sealed envelope. This system will randomly allocate the participant to either the intervention or control arm. The unblinded researcher will notify the befriending service and participants with ID of their allocation.

Randomisation will be blocked using randomly varying block sizes, stratified by centre. The allocation schedule will be concealed through the use of this central web-based randomisation service. The randomisation protocol will be created by the trial statistician and the set-up of the service will be overseen by the Priment Clinical Trials Unit.

### Intervention group

Participants with ID will meet with the volunteering coordinator to obtain information about their hobbies and interests and activities they would like support to participate in. Based on this information, participants with ID will be matched to a volunteer who can accommodate the person’s interests.

#### Befriending intervention

The befriending intervention has been adapted from the existing models used by the two participating befriending services and from other studies of befriending.^26 30^ The purpose of the befriending relationship will be to provide friendship and emotional support, and to assist the individual to access activities in the community that they may be unable to do alone. As participants become more confident, they will be encouraged to access activities in the community on their own in order to promote sustained social activities beyond the befriending relationship.

The volunteer (befriender) and person with ID will meet once a week for at least 1 hour, for 6 months, although some breaks are anticipated due to holidays or illness. They will receive a booklet detailing local activities and amenities, which they can use to plan activities. The emphasis will be on assisting the individual to make choices about the activities that they wish to pursue. The volunteer is not expected to carry out personal care, administer medication or accompany the individual to medical appointments. Contacts by phone/social media can take place, in addition to face-to-face contacts. The pair can spend some sessions in the person’s home, but this should not exceed 50% of the total number of sessions. Sessions may take place during evenings/weekends, depending on the pair’s availability. They will keep a record of their activities in a structured log that will be provided (whether they attended each session, reasons for cancellation, what they did in each session and duration of activity) and record of other types of contact. Volunteers will be reimbursed travel expenses, but other expenses will need to be agreed with the befriending service. Participants with ID will not be reimbursed travel expenses or the costs of activities.

#### Introduction and monitoring of the befriending relationship

The volunteering coordinator will arrange a face-to-face meeting where the pair will be introduced to each other. If they agree to continue, the pair will arrange to meet on their own; if they decide that the pairing is unsuitable, they will be rematched. If the volunteer or individual with ID drops out of the relationship once it has become established, attempts will be made to rematch them. Volunteers may be matched to more than one participant with ID.

The volunteering coordinator will arrange a face-to-face meeting with the pair after 6 weeks and will maintain contact with each person by telephone/face-to-face contact every 4 weeks thereafter to monitor the progress of the relationship. A further meeting will be held with the pair at the end of the 6 months to obtain general feedback about the befriending intervention, to discuss ending the relationship and to support the individual with ID with coming to terms with the ending. The pair may continue their relationship if they wish after the 6-month period, but arrangements for monitoring the relationship will vary, depending on the befriending service. Information will be obtained on any relationships continuing beyond 6 months and the monitoring that has been provided.

#### Training and supervision of volunteers

The volunteers will attend training delivered face-to-face and as e-learning. The training will cover the benefits of befriending and issues related to confidentiality and lone working; advice on how to plan meetings effectively; health and safety; safeguarding; learning disability awareness; and professional boundaries, which covers dealing with sensitive issues, ending relationships and expectations of the role of the volunteer. Volunteers will also receive slides and a manual developed by the research team, with information about the study and additional information about communication, challenging behaviour and mental health problems.

Volunteers will have access to group or individual supervision delivered face-to-face or over the phone, once a month, by the volunteer coordinator, which will address issues that may have arisen from the relationship, for example, concerns about mental health or behaviour.

#### Training and support for befriending services

Participating befriending services will complete good clinical practice (GCP) training and will undergo training on the study research processes and procedures as part of the site initiation visit. Volunteer coordinators will receive support from the research team through regular email and telephone contact, and they will attend Trial Management Group (TMG) meetings.

### Control group

Participants in the control arm will receive the activities booklet. They will meet with a member of the research team who will discuss the booklet with them (and their carer, if present) and encourage them to engage with activities. This is to control for the effects of participants in the treatment arm receiving more information about local activities.

Both the control and intervention arms will also have access to ‘usual care’. This will include access to multidisciplinary input from community ID services. Participants can continue to take their usual medication and can access other community and hospital health services and day services. Information about usual care will be collected as part of the baseline assessment.

### Outcomes

#### Recruitment and retention of participants

We will examine the proportion of participants with ID recruited from among those eligible, the proportion of volunteers recruited from among people expressing an interest over a 6-month period, the proportion of participants with ID who are successfully matched with a volunteer, the proportion of participants with ID and volunteers who drop out of the intervention arm and the proportion of participants and volunteers who complete subsequent follow-up assessments.

#### Adverse events

Adverse events will be collected at each follow-up assessment using open-ended questions and will also be reported directly to the chief investigator by the befriending services, including concerns about safeguarding. Volunteers will follow a protocol if they have concerns about the participant’s mental health, which will involve informing the volunteer coordinator, who will in turn notify the CI and the referring clinician or a health professional involved in the person’s care. If a serious incident (eg, self -harm and challenging behaviour) occurs out of hours, the carer will be notified and emergency services will be contacted if appropriate. All adverse events will be recorded in the medical records and Case Report Forms. Serious adverse events (eg, safeguarding concerns and hospitalisation) will be recorded in the serious adverse effects log.

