## Aims and objectives

The main aim of the study was to determine the feasibility and acceptability of a full-scale RCT of one-to-one befriending by volunteers for people with ID in addition to usual care, compared with an active control arm.

The objectives were to

Examine the recruitment and retention of individuals with ID and volunteers in the trial and the number of successfully matched pairs within the 6-month study recruitment period.Record any negative consequences/adverse effects of befriending.Measure the extent to which the intervention is delivered as intended by volunteers and the befriending schemes.Examine the acceptability of the intervention and study procedures by exploring the views of individuals, volunteers, carers and befriending services.Examine changes in health and social outcomes by carrying out exploratory analyses of the impact of befriending on depressive symptoms measured by the Glasgow Depression Scale^28^ at 12 months and other outcomes (psychological distress, self-esteem, loneliness, quality of life and social participation) at 6 and 12 months postrandomisation.Carry out exploratory analyses of the impact of befriending on volunteers’ well-being, self-esteem, loneliness and attitudes towards people with ID at 6 and 12 months.Estimate the sample size required and determine the final trial design for a full-scale RCT.Assess the feasibility of collecting data that would inform a future analysis of cost effectiveness.

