## Discussion

This is the first pilot RCT of one-to-one befriending, monitored by community befriending services, in people with ID. The trial will provide data on whether a full trial will be feasible, in terms of recruitment and retention of volunteers and people with ID and data on potential beneficial and adverse effects, acceptability and the extent to which the intervention is delivered as intended by volunteers and the befriending services. It will help to inform modifications that need to be made to enable a future trial to overcome barriers and challenges that may be encountered in this pilot.

There is currently limited evidence supporting the choice of a primary health outcome, but the use of depressive symptoms is supported by one systematic review.^24^ This pilot study will help to determine whether measuring depressive symptoms is the most appropriate primary outcome for a future trial.

One of the main challenges of this study will be to ensure that the intervention and the recruitment, training and supervision of volunteers are carried out according to the trial protocol as these aspects vary between befriending services, and was an issue in a recent trial of befriending in people with psychosis.^25^ While both befriending services have committed to the study, there are resource implications for these services as the intervention costs are not covered by the research funding. External factors such as funding cuts to these services could influence the delivery of the intervention and the success of the trial. The process data will allow us to examine whether a future trial would need to be more pragmatic and whether the befriending intervention should permit more flexibility.

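### Adverse events have an extra, scheduled reporting route only in the befriending arm, so a by-arm summary that pools all sources would tend to over-count events with befriending

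*Protocol article*

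**What the plan says.** The Adverse events section of the protocol article sets out three routes.

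- **Both arms:** "Adverse events will be collected at each follow-up assessment using open-ended questions". Table 1 places an adverse effects review at both follow-up assessments, which are done by a research assistant blind to allocation.
- **Through the services:** events "will also be reported directly to the chief investigator by the befriending services", and this expressly covers safeguarding concerns.
- **Through the volunteers:** "Volunteers will follow a protocol if they have concerns about the participant’s mental health", with the volunteer coordinator then informing the chief investigator.

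The same section sends all events to the medical records and case report forms, and serious events to a log. It gives safeguarding concerns as an example of a serious event.

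Scheduled contact in the intervention arm is described elsewhere. The pair meets weekly for 6 months (Befriending intervention). The coordinator sees the pair at 6 weeks and then "will maintain contact with each person by telephone/face-to-face contact every 4 weeks thereafter", and "A further meeting will be held with the pair at the end of the 6 months" (Introduction and monitoring). Volunteers have access to monthly supervision (Training and supervision of volunteers). Under Control group, controls receive the booklet, a meeting with a researcher to discuss it, and usual care.

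The objective is worded "Record any negative consequences/adverse effects of befriending". The Discussion says the trial will provide "data on potential beneficial and adverse effects". The Analysis section summarises participants' outcomes descriptively by arm and confines modelled effects to health and social outcomes.

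**The concern.** A count of recorded events depends on how often they happen and on how many chances there are to record them. Here the second factor differs by arm. An event in an intervention participant can be noticed by the volunteer, the coordinator or the assessor; in a control, the described route is recall at an assessment about 6 months after the previous one. Serious events are exposed too, because safeguarding concerns are both something the services report and an example of a serious event.

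The article does not say that sources will be kept apart when events are summarised. Adverse events sit under the Outcomes heading and outcomes are to be summarised by arm, so an all-source table by arm is a natural product. Read at face value, it could make befriending look more harmful than it is. A procedure tried out in a pilot may also carry over to a full trial, where larger numbers would not remove the bias.

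**Working it through.** The article gives no event rate, capture probability or harms estimate, so there is no stated figure to reproduce. What can be checked is the number of contacts and the direction of the bias.

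**Scheduled contacts**

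| Contact | Befriending | Control |
|---|---|---|
| Follow-up assessments with adverse-event questions | 2 | 2 |
| Coordinator contacts (weeks 6, 10, 14, 18, 22, 26) | about 6 | none described |
| Weekly volunteer visits over about 26 weeks | up to about 26 | none |

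The 26 visits are a ceiling: the article expects breaks, and its adherence measure counts volunteers with at least 10 sessions.

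**Illustration (all capture values are assumptions)**

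Let *p* be the true risk, equal in both arms; *r* the chance that the follow-up questions capture an event; *s* the chance that the service route captures it, independently; and *f* the share of events that fall while that route is active.

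- Control, recorded risk: *p r*
- Befriending, all sources pooled: *p* [*r* + *f s*(1 − *r*)]
- Ratio: 1 + *f s*(1 − *r*)/*r*
- Difference: *p f s*(1 − *r*)

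With *f* = 1 the ratio equals [1 − (1 − *r*)(1 − *s*)]/*r*. With *f* = 0.5 the route covers only the 6 intervention months of 12, with events spread evenly.

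| *r* | *s* | Ratio, *f* = 1 | Ratio, *f* = 0.5 |
|---|---|---|---|
| 0.9 | 0.25 | 1 + 0.25 × 0.1/0.9 = 1.03 | 1.01 |
| 0.7 | 0.5 | 1 + 0.5 × 0.3/0.7 = 1.21 | 1.11 |
| 0.5 | 0.5 | 1 + 0.5 × 0.5/0.5 = 1.50 | 1.25 |
| 0.5 | 0.75 | 1 + 0.75 × 0.5/0.5 = 1.75 | 1.38 |

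The ratio exceeds 1 whenever *f s* > 0 and *r* < 1, so only the size depends on the assumptions.

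**In participants.** Take 20 per arm (40 recruited, 1:1, as in Sample size), *p* = 0.4, *r* = 0.7 and *s* = 0.5. Controls with a recorded event: 20 × 0.4 × 0.7 = 5.6. Befriending: 20 × 0.4 × 0.85 = 6.8 with *f* = 1, or 20 × 0.4 × 0.775 = 6.2 with *f* = 0.5.

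**Against sampling error.** With *f* = 1, *p* from 0.2 to 0.4, *r* from 0.5 to 0.9 and *s* from 0.25 to 0.75, the spurious difference runs from 0.2 × 0.25 × 0.1 = 0.005 to 0.4 × 0.75 × 0.5 = 0.15. The 95% CI half-width for a risk difference with 20 per arm is 1.96 × √(2 × 0.2 × 0.8/20) = 0.25 at *p* = 0.2, and 0.30 at *p* = 0.4.

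**Common route only.** Counting only events elicited at follow-up gives *p r* in both arms, a ratio of 1.00 in every scenario if recall is equal.

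**The case against.** The strongest reply is that the criticism is aimed at an analysis the article does not state. The aim is to record adverse effects of befriending, and closer surveillance of that arm suits it. Effect estimates are limited to health and social outcomes, no progression rule rests on a difference in harms, and nothing says that sources are pooled or that the source goes unrecorded. Tabulation may be settled in the full protocol or analysis plan. This stands, and it makes the point conditional.

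Other parts of the reply also carry weight. Both arms complete the service-use inventory and a medication review at both follow-ups, so a control's hospital stay could surface there as well. Coordinator contacts are meant to follow the relationship and are not described as eliciting adverse events. Some controls may already be known to the services, since recruitment draws on their referrals, although no scheduled contact or reporting is described for them. In a trial this small, the illustrated bias is below the sampling error.

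Three stronger readings are tempting, and the document does not support them.

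- **That every comparison of harms between arms is biased.** The follow-up questions use one schedule and a blinded assessor in both arms, so a comparison confined to them avoids this asymmetry.
- **That the adverse-event questions unblind the outcome scales.** No question order is fixed, Table 1 lists the review after the scales, and the social support and participation scales could reveal a befriender just as easily.
- **That harm to volunteers would be missed.** Table 2 has no adverse-effects item, but volunteers complete well-being, self-esteem and loneliness scales, have supervision, and have drop-out reasons recorded where possible. The process evaluation looks for unintended consequences and samples volunteers whose relationships broke down.

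**Conclusion.** The point holds as a conditional one. The difference in ascertainment is in the text, and with equal true rates and equal recall its direction is fixed: pooling all sources inflates recorded events with befriending. Whether it affects a result depends on how the by-arm summary is built, which the article leaves open.

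The size cannot be derived from the document. The range of about 1.01 to 1.75 rests wholly on assumed capture values, independent capture by the two routes, and an assumed period of coverage. It should not be cited as an estimate. This is an inexpensive improvement to reporting, with no fault implied in the safety surveillance.

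**What to change.** Keep every safety-reporting route as it is. Then:

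1. Add a source field to the adverse-event form: elicited at assessment, reported by the service, reported by the volunteer. Allow more than one entry, so that an event already reported by the service still counts as elicited if it also emerges at the assessment.
2. State that any by-arm summary of adverse or serious adverse events uses only those elicited at the 6- and 12-month assessments, with the same questions in both arms.
3. List service- and volunteer-reported events separately, with relatedness. This also serves the objective of recording adverse effects of befriending.

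The cost is one form field and a split table. The drawback is that the by-arm summary omits events known only through the services or volunteers; these still appear in the separate listing. The comparison continues to assume equal recall in the two arms.

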#### Acceptability of the intervention

This will be informed by data on retention/drop-out of volunteers and participants, the extent of engagement with the intervention by participants and volunteers (based on number of sessions attended) and qualitative data obtained from volunteers, participants with ID, carers of people with ID and staff from the befriending service.

